# PROTECTOR / FIRE‑10: study protocol for a prospective, randomized, open-label, multicenter phase III trial to investigate the efficacy of preoperative systemic therapy in advanced colon cancer

**DOI:** 10.1186/s12885-026-15682-3

**Published:** 2026-03-20

**Keywords:** Colon cancer, Colorectal cancer, Preoperative chemotherapy, Neoadjuvant therapy, Colorectal surgery

## Abstract

**Background:**

Standard of care for non-metastatic colon cancer is surgery followed by stage-guided adjuvant therapy and/or structured follow-up. Upfront surgery in resectable colon cancer is irrespective of local T/N stage, whereas adjuvant systemic therapy is recommended according to pathological staging. The role of neoadjuvant chemotherapy remains unclear. Whereas perioperative systemic therapy in colon cancer seems to be safe and may lead to pathologic downstaging, evidence on improved survival and quality of life remains scarce. The PROTECTOR / FIRE‑10 trial aims to generate evidence that perioperative systemic therapy improves survival without compromising quality of life in locally advanced, mismatch-repair proficient colon cancer patients.

**Methods and design:**

Open-label, randomized, controlled, multicenter, phase III study with two parallel arms. Patients with locally advanced colon or upper rectal cancer staged cT3-4 and/or cN+ are randomized in a 2:1 fashion (favoring preoperative therapy) to investigate the efficacy, patient reported quality of life, and safety of preoperative therapy followed by surgery (Arm A) versus direct surgery followed by non-study specific stage-guided adjuvant therapy (Arm B). Stratification during randomization will be performed according to the following parameters: Fit for mFOLFOXIRI vs. mFOLFOX/CAPOX vs. 80%-mFOLFOX/CAPOX, ECOG 0 vs. ECOG 1-2, and left-sided primary vs. right-sided primary tumor. Only patients with confirmed mismatch-repair proficient and/or microsatellite stable tumor can be included.

Preoperative treatment in Arm A is performed for a maximum of 6 biweekly cycles of FOLFOX/FOLFOXIRI or for a maximum of 4 triweekly cycles CAPOX (i.e., appr. 12 weeks). Patients in both arms should undergo quality-controlled surgery of the primary tumor, performed as complete mesocolic excision.

Patients will be followed up with regard to relapse, survival and if applicable subsequent anti-cancer treatments until death or for at least 5 years after randomization, whichever date is earlier.

**Discussion:**

The PROTECTOR / FIRE‑10 trial compares preoperative systemic therapy to upfront surgery (with stage-guided adjuvant therapy) in patients with locally advanced colon cancer.

**Trial registration:**

This study is registered with clinicaltrials.gov (NCT06899477) and EudraCT (2023-508076-11-00).

**Supplementary Information:**

The online version contains supplementary material available at 10.1186/s12885-026-15682-3.

## Background

Colorectal cancer is the third most common cancer diagnosed in women and men, it was the fourth-leading cause of cancer death in both men and women younger than 50 years in the late-1990s but is now first in men and second in women [1]. In Germany, approximately 55,000 to 60,000 new cases are diagnosed annually [2]. Colon cancer accounts for two thirds of all colorectal cancer cases.

In patients with colon or upper rectal cancer, irrespective of the assumed T/N-stage, the standard of care in the absence of metastases is surgery, which is followed by stage-guided adjuvant therapy and/or structured follow-up [3]. Adjuvant therapy is clearly indicated in UICC stage III patients (nodal positive) and also recommended in some patients with UICC II (T3-4, N0 tumors) with respective risk criteria (T4 tumors, emergency surgery, perforation, insufficient lymph node harvest etc.) [3, 4].

The strategy of neoadjuvant or perioperative systemic therapy represents an emerging concept in solid tumors and is already a standard of care in some gastrointestinal cancers such as advanced gastric and esophageal junction cancer, and notably in advanced lower rectal cancer [5–8]. Concepts addressing the lower rectal cancer, biologically similar to colon cancer, include total neoadjuvant therapy (TNT) as a new standard of care [7, 8]. Potential benefits of neoadjuvant therapy for patients, contributing to improved long-term outcome, include:

Population effect: nearly 100% exposition to chemotherapy vs. only those patients that are fit enough to receive chemotherapy after resection.Earlier treatment of micrometastases.Downstaging of the primary tumor, enabling easier resections.Pre-habilitation before radical surgery.

In locally advanced colon cancer, two phase III trials have investigated perioperative treatment with 6/12 weeks of systemic therapy before surgery, in both cases doublet therapy with FOLFOX/CAPOX. The FOXTROT trial was first presented at the 2019 ASCO congress with lacking anticipated event rates and was consecutively rated “negative” with a borderline-significant *p*-value. This was despite exactly hitting the predefined effect size. In summary, FOXTROT suggested that perioperative therapy in colon cancer is safe and might be beneficial in terms of disease-free survival and overall survival [9].

The OPTICAL trial investigated perioperative therapy with 3 months of FOLFOX/CAPOX before and after surgery as experimental arm and reported a trend towards better disease-free survival, that was comparable to the effect size in FOXTROT together with a significant effect on overall survival (secondary endpoint) [10].

In order to further develop the encouraging signals of the FOXTROT and OPTICAL trial and the currently implemented TNT in rectal cancer into a new standard of care for colon cancer, our study will include necessary modifications in the design as follows:

Exclusion of dMMR/MSI tumors as these derived no benefit in the FOXTROT and OPTICAL trial [9, 10].Escalation of the treatment duration from 6 to 12 weeks in accordance with current concepts in rectal cancer to ensure more efficacy.Option to escalate therapy regimens (i.e., mFOLFOXIRI) [7, 8].Surveillance of T- and N- stages in the standard arm to ensure that the frequency of over-staged tumors in the trial can be controlled and does not affect the necessary event-size.

Together, with these modifications, the PROTECTOR / FIRE‑10 study will refine the clinical and oncological benefits of using preoperative systemic therapy in advanced colon cancer.

## Methods/design

### Aim of the study

The main objective of this randomized multicenter trial is to generate further evidence that preoperative chemotherapy improves disease-free survival in patients with advanced colon or upper rectal cancer.

### Study setting and trial population

PROTECTOR / FIRE‑10 is an investigator-initiated prospective randomized open-label multicenter phase III trial with two parallel study groups. The trial is organized by the Charité - Universitätsmedizin through the German Alliance “Arbeitsgemeinschaft Internistische Onkologie (AIO)” for Clinical Cancer Trials, sponsored by the Deutsche Krebshilfe (German Cancer Aid).

Patients with colon or upper rectal (above 12 cm form anal verge) cancer staged cT3-4 and/or cN + and eligible for curative surgery will be included in the trial.

See Fig. 1 for an illustration of the study design.

**Fig. 1 Fig1:**
[figure not shown]
Illustration of Trial Design. (CT = computed tomography; R = randomization; MDT = multidisciplinary tumor board; DFS = disease free survival)

### Sample size

Based on the best available evidence described above [9, 10], 2-year DFS rate is 70% in the straight to surgery group and we hypothesize that DFS rate will be 78% in the neoadjuvant treatment followed by surgery group. To demonstrate an increase of 8% points in 2-year DFS rate (hazard ratio = 0.696), it is required to observe 271 DFS events, with the recruitment of 714 (476:238 per arm) patients with an allocation ratio of 2:1 (experimental vs. standard). These calculations assume that the DFS time follows a piecewise exponential distribution with two strata within the maximum follow up time ([0–2] years [2–8], years). For the first stratum, we assume that DFS rate will be 70% after 2 years in the control group. For the second stratum, we expect a level-off effect to a plateau of 60% DFS rate after 8 years. The sample size was calculated with 2-sided 5% level of significance, 80% power, with 5-year recruitment and 5-year follow-up periods and 5% drop-out in the first two years. The event rate in the straight to surgery group will be monitored annually by the independent data monitoring and ethics committee to ensure the baseline assumptions are appropriate. An interim analysis for efficacy will not be conducted. Given that an inferiority is unlikely with the background of TNT concepts in rectal cancer and previous trials and the increased sample size would impact on the feasibility of recruitment, interim analyses will solely focus on safety.

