### Statistical analyses

#### Primary analysis

The null hypothesis to be tested in confirmatory analysis states that the hazard ratio for DFS comparing intervention versus control equals 1. This hypothesis will be tested by means of piecewise exponential model, by dividing the maximum follow-up time in 2 strata (0–2 years, 2–8 years), assuming the hazard is approximately equal in each time interval. This regression will be adjusted for the strata for randomization mentioned above. The two-sided significance level is set to 0.05. The primary analysis will be conducted based on the full analysis set which is defined as the intention to treat population. In a survival analysis setting, missing values are treated as non-informative censoring values so there is no need for imputation. 

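### 714 patients are expected to give about 226 DFS events in the stated 5+5 years, not the required 271, so power is about 73% on the natural reading of the assumptions

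*Protocol article*

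**What the plan says.** All inputs are in the Sample size section of the protocol article.

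- Control arm: "2-year DFS rate is 70% in the straight to surgery group".
- Effect to be shown: a 2-year DFS of 78% in the experimental arm, which the article gives as a hazard ratio of 0.696.
- Error rates: "2-sided 5% level of significance, 80% power".
- Size: "it is required to observe 271 DFS events, with the recruitment of 714 (476:238 per arm) patients", allocated 2:1 in favour of the experimental arm.
- Shape of the DFS curve: piecewise exponential with a cut at 2 years and a maximum of 8 years. The sentence on the first interval names the control group. The next one says "we expect a level-off effect to a plateau of 60% DFS rate after 8 years" and names no arm.
- Timeline: "with 5-year recruitment and 5-year follow-up periods and 5% drop-out in the first two years".
- Safeguard: "The event rate in the straight to surgery group will be monitored annually by the independent data monitoring and ethics committee".

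The Primary analysis section tests one hazard ratio for DFS in a model built "by dividing the maximum follow-up time in 2 strata", 0–2 and 2–8 years. The article does not show how 271 events became 714 patients.

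**The concern.** To see 271 events among 714 patients, 271/714 = 38.0% of all patients must have an event. That is close to what the control arm alone would show (40% by 8 years, a little less after drop-out). Two thirds of the patients, however, are in the arm assumed to have a hazard ratio of about 0.70, where only about 30% would have an event by 8 years. The printed figures therefore appear to disagree with each other.

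At stake is the stated power of the confirmatory test. The Background recalls that an earlier trial in this setting was rated negative after too few events, although it hit its predefined effect size. Here a shortfall would be built into the plan. The annual check would not reveal it, because it looks at the control arm, which can be exactly on target while the total falls about 45 events short.

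**Working it through.** **1. Required events (reproduces).** HR = ln 0.78 / ln 0.70 = 0.6966. Schoenfeld formula with 2:1 allocation:

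(1.960 + 0.842)² / [(2/3)(1/3)(ln 0.6966)²] = 270.2, rounded up to 271. With HR rounded to 0.696 it is 269.

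**2. Hazards, with 60% as control-arm DFS at 8 years.**
- Control, years 0–2: −ln 0.70 / 2 = 0.1783 per year.
- Control, after year 2: −ln(0.60/0.70) / 6 = 0.0257 per year.
- Experimental: both multiplied by 0.6966, so 8-year DFS = 0.60^0.6966 = 0.701.
- Drop-out, years 0–2 only: δ = −ln 0.95 / 2 = 0.0256 per year.

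**3. Expected events.** For a patient with follow-up F, the event probability is

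λ₁/(λ₁+δ) × [1 − e^(−2(λ₁+δ))] + e^(−2(λ₁+δ)) × [1 − e^(−λ₂(F−2))],

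averaged over F uniform on 5 to 10 years (5 years of recruitment, assumed uniform, plus 5 years of follow-up).
- Control: 0.380 × 238 = 90.5.
- Experimental: 0.284 × 476 = 135.1.
- Total: 225.6.

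**4. Power.** Φ(√(225.6 × 2/9) × 0.3615 − 1.960) = 0.726. Two simulations of the two-piece exponential test gave 73.5% (4,000 trials) and about 74.5% (8,000 trials). No simulated trial reached 271 events.

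**5. Does the result hang on a detail?** Same hazards, 714 patients:

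| Variant | Events | Power |
|---|---|---|
| Stated design | 226 | 73% |
| Time axis stopped at 8 years | 222 | 72% |
| No drop-out | 233 | 74% |
| Everyone followed 8 years, no drop-out | 238 | 75% |
| Everyone followed 10 years, no drop-out | 257 | 78% |

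The last row is more than the 5+5 plan allows and is still below 271. Reaching 271 would take about 858 patients (858 × 225.6/714 = 271.1), or about 10 years of follow-up after the last patient (269.6 events with 714).

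**6. Where 714 may come from.** 271/(0.40 × 0.95) = 713.2, which becomes 714 at 2:1. Likewise, the calculation in step 3 with no treatment effect gives 271.4 events. Both use a single event fraction for all patients.

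**7. Other readings of the 60%.**
- Both arms at 60% at 8 years: the hazard ratio after year 2 would be ln(0.60/0.78) / ln(0.60/0.70) = 1.70, against the single ratio that is planned and tested.
- No effect after year 2: 239 events.
- Trial-wide DFS of 60%: solving S/3 + (2/3)S^0.6966 = 0.60 gives control 52.4% and experimental 63.8%. Under 5+5 years with drop-out: 267.5 events, power 79.6%. With the time axis stopped at 8 years: 261.5 events, 78.7%. With everyone followed 8 years: 275.9 events, 80.8%.

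**The case against.** The strongest reply is that the plateau sentence names no arm. Read as the DFS of the whole trial, 60% at 8 years is compatible with one hazard ratio in both intervals and gives about 267 events and about 80% power, close to what is claimed. This stands as a coherent alternative, and it means that the origin of 714 cannot be asserted as fact. It is nevertheless strained. The sentence continues a specification that begins with the control group, and the implied control DFS of about 52% at 8 years appears nowhere in the article. Under the stated timeline it also ends slightly below 271.

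A reader might infer that 714 patients can never produce 271 events. The documents do not support that. The abstract sets 5 years from randomisation as a minimum, and the Structured follow-up section continues survival follow-up afterwards, so later events would add to the count. The calculation already gives each patient 5 to 10 years, and the sample size plans nothing longer. The supportable statement is that 271 events are not expected within 5+5 years.

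A reader might also infer that the analysis is triggered by the 271st event. Neither the Sample size nor the Primary analysis section says so; 271 is given as the number needed for power.

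Finally, the loss is moderate: about 5 to 7 points of power, and the mismatch between 8 and 10 years alone changes the count only from 226 to 222.

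**Conclusion.** The point holds for the pairing of 271 events with 714 patients. The 271 is right. On the natural reading, 714 patients are expected to yield about 226 events in the stated period, about 45 short, and power at HR 0.697 is about 73% by the formula that reproduces the 271, or 73% to 75% by simulation. This rests on 60% being the control arm's 8-year DFS, a constant hazard ratio, uniform accrual, and drop-out confined to the first two years. Accrual pattern and drop-out handling do not rescue it, since 10 full years for every patient without drop-out gives 257 events.

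The use of one 40% event fraction for both arms is a likely explanation, not a demonstrated one. If a trial-wide plateau was meant, power is about 80%, but the text as it stands does not convey the control-arm rate then assumed. On either reading the section needs correction.

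**What to change.** 1. In the Sample size section, do one of two things. Either state that 714 patients over 5+5 years are expected to give about 226 DFS events and about 73% power for HR 0.697, with 80% power at HR about 0.67 (2-year DFS 70% against about 78.7%; the event count is recalculated at that ratio, about 221). Or, if 60% was meant for the whole trial, say so and print the implied 8-year rates of about 52% (control) and 64% (experimental). In both cases show the step from events to patients.
2. State that the primary analysis takes place at the planned end of follow-up, and do not make it wait for 271 events within the 5+5-year plan.
3. Let the second model interval run from 2 years to the end of follow-up, because 5+5 years allows up to 10 years of observation against the stated 8.
4. Have the monitoring committee track the pooled event count as well as the control-arm rate.

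The cost is a change of wording and, on the natural reading, a less favourable stated power. No additional patients are required.

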### Inclusion criteria

Participants are eligible to be included in the trial only if all of the following criteria apply at time of enrollment:

Patient’s signed informed consent.Patient’s age ≥ 18 years at the time of signing the informed consent.Histologically confirmed adenocarcinoma of the colon or upper rectum.Confirmed mismatch-repair proficient and/or microsatellite stable tumor. Both immunohistochemistry and PCR can be used for diagnosis.Intent for curative surgery.Predicted (clinical) T3 or T4 stage and or nodal positivity (N+) assessed by the local study team based on computed tomography and/or magnetic resonance imaging of the abdomen and pelvis. The imaging criteria were adjusted to achieve a low false positive rate.T3-4 defined as unequivocal signs of invasion of surrounding tissue structures or organs N+ defined as regional (within drainage territory of the primary site) lymph node(s) without fat hilus or occupying calcifications enlarged to a short/long axis diameter of ≥1/1.5 cm (for ileocecal region ≥ 1.3/1.8 cm)Absence of clear distant metastases assessed by the investigator based on respective routine evaluations within 6 weeks prior to inclusion into the trial (Preferred: computed tomography of thorax and abdomen. Alternatively, magnetic resonance images, FDG-PET, sonography and x-rays might be used for assessment).Absence of significant active wound healing including severe chronic non-healing wounds, ulcerous lesions or untreated bone fracture.ECOG performance status 0-2.Adequate bone marrow, hepatic and renal organ function, defined by the following laboratory test results:Absolute neutrophil count ≥ 1.5 x 109/L (1,500/µL).Hemoglobin ≥ 80 g/L (8 g/dL) with or without transfusion.Platelet count ≥ 100 x109/L (100,000/µL) without transfusion.Total serum bilirubin of ≤ 1.5 x upper limit of normal (ULN).Aspartate aminotransferase (AST) ≤ 3.0 × ULN.Calculated glomerular filtration rate (GFR) according to Cockcroft-Gault formula or according to MDRD ≥ 50 mL/min or serum creatinine ≤ 1.5 x ULN.Patients without anticoagulation need to present with an INR < 1.5 x ULN and PTT < 1.5 x ULN. Patient with prophylactic or therapeutic anticoagulation are allowed into the trial.Proficient fluorouracil metabolism as defined:Prior treatment with 5-FU or capecitabine without unusual toxicity or,If tested, normal DPD deficiency test according to the standard of the study site, orIf tested, in patients with DPD deficiency test with a CPIC activity score of 1.0-1.5 fluoropyrimidine dosage should be reduced by 50% and patients are allowed into the trial.For women of childbearing potential (WOCBP): negative pregnancy test within 7 days before treatment initiation and agreement to remain abstinent (refrain from heterosexual intercourse) or use contraceptive methods with a failure rate of < 1% per year during the treatment period and for at least 6 months after the last dose of study treatment.

For men: With female partners of childbearing potential, men must remain abstinent or use a condom plus an additional contraceptive method that together result in a failure rate of < 1% per year during the treatment period and for 6 months after the last dose of study treatment. Men must refrain from donating sperm during this same period.

With pregnant female partners, men must remain abstinent or use a condom during the treatment period and for 6 months after the last dose of study medication to avoid exposing the embryo.

## Exclusion criteria

Participants are excluded from this trial if any of the following criteria apply at time of enrollment:

Malignant intestinal obstruction or directly imminent obstruction as assessed by the local study team. Patients with treated and resolved obstruction are allowed into the trial.Previous chemotherapy for colorectal cancer of any stage.New York Heart Association Class III or greater heart failure by clinical judgement.Myocardial infarction within 6 months prior to randomization; percutaneous transluminal coronary angioplasty (PTCA) with or without stenting within 6 months prior to randomization.Unstable angina pectoris.Unstable cardiac arrhythmia > grade 2 NCI CTCAE despite anti-arrhythmic therapy.Ongoing toxicities > grade 2 NCI CTCAE, in particular peripheral neuropathy.Active uncontrolled infection by investigator’s perspective.Known hypersensitivity to 5-FU, folinic acid, capecitabine, irinotecan or oxaliplatin or to any of the other excipients listed in Sect. 6.1 of the corresponding SmPC.Recent or concomitant treatment with brivudine.Peripheral sensitive neuropathy with functional impairment (> grade 1 acc. to CTCAE version 5.0.Simultaneous application of St. John’s Wort preparations.Pernicious or other megaloblastic anemia caused by vitamin B12 deficiency.Major surgical procedure, open biopsy, or significant traumatic injury within 21 days prior to randomization that may interfere with systemic therapy as judged by the investigator.Any other disease, metabolic dysfunction, physical examination finding, or clinical laboratory finding that contraindicates the use of an investigational drug, may affect the interpretation of the results, or may render the patient at high risk from treatment complications, including but not limited to:Simultaneous application of live vaccines during treatment with irinotecan and for at least 6 months after the last dose.5-FU must not be given in combination with brivudin, sorivudin and analogues to patients homozygous for DPD and patients known with completely missing DPD activity.Severe diarrhea.Medical history of malignant disease other than colorectal cancer with the following exceptions:patients who have been disease-free for at least three years before randomizationpatients with adequately treated and completely resected basal cell or squamous cell skin cancer, in situ cervical, breast or prostate cancer, stage I uterine cancerpatients with any treated or untreated malignant disease that is associated with a 5-year survival prognosis of ≥ 90% at the time of inclusion (assessed and documented by the investigator) and does not require active therapyKnown alcohol or drug abuse.Pregnant or breastfeeding females.Participation in a clinical trial or experimental drug treatment within 28 days prior to potential inclusion in the clinical trial or within a period of 5 half-lives of the substances administered in a clinical trial or during an experimental drug treatment prior to potential inclusion in the clinical trial, depending on which period is longest, or simultaneous participation in another clinical trial while taking part in this clinical trial.Patients depended on Sponsor, investigator or study site.Patient committed to an institution by virtue of an order issued either by the judicial or the administrative authorities.Limited legal capacity.
